## Abstract

The world-wide rise in obesity parallels growing concerns of global warming and depleting natural resources. These issues are often considered separately but there may be considerable benefit to raising awareness of the impact of dietary behaviours and practices on the food supply. Australians have diets inconsistent with recommendations, typically low in fruit and vegetables and high in energy-dense nutrient-poor foods and beverages (EDNP). These EDNP foods are often highly processed and packaged, negatively influencing both health and the environment. This paper describes a proposed dietary assessment method to measure healthy and sustainable dietary behaviours using 4-days of food and beverage images from the mobile food record (mFR) application. The mFR images will be assessed for serves of fruit and vegetables (including seasonality), dairy, eggs and red meat, poultry and fish, ultra-processed EDNP foods, individually packaged foods, and plate waste. A prediction model for a *Healthy and Sustainable Diet Index* will be developed and tested for validity and reliability. The use of the mFR to assess adherence to a healthy and sustainable diet is a novel and innovative approach to dietary assessment and will have application in population monitoring, guiding intervention development, educating consumers, health professionals and policy makers, and influencing dietary recommendations.

## 1. Introduction

Recent evidence would suggest that eating a diet that increases environmental sustainability has the potential to also benefit health [1,2,3,4]. Worldwide overweight and obesity rates are rising, posing significant costs at an individual and societal level [5]. In Australia, the direct cost spent annually on overweight and obesity is estimated to be at least $21 billion [6]. The overconsumption of kilojoules above an individual’s energy requirements (resulting in weight gain) is environmentally unsustainable and places burden on the future food supply [7]. Hence, there may be considerable health and environmental benefits in assessing the impact of dietary behaviours and practices on the food supply [8,9]. Research on the effects of diet on the environment is rapidly emerging, particularly the area of life cycle assessment- a method for measuring the carbon footprint (amount of greenhouse gas emissions) of food products throughout production [10,11]. However, identifying a healthy and sustainable diet that meets the nutrient requirements of all populations groups and cultures is complex and challenging [1,8,12,13]. Researchers have identified the need to identify dietary patterns that provide adequate nutrition at a low environmental cost [14], but methods to do so have focused on the assessment of typical diets and food choices at a population level [2,13] rather than individual dietary behaviours. Therefore, there is limited evidence on whether current individual dietary patterns align with a sustainable diet.

The Australian Dietary Guidelines, which provide the evidence-base for dietary recommendations and directions for nutrition policy in Australia, have highlighted the issue of food, nutrition and environmental sustainability over the last decade. The 2013 review of the Guidelines sought to assess the evidence to make dietary recommendations that were protective of health as well as the environment. However, no specific guidelines to address a sustainable diet were made as a result of inadequate evidence in the area, rather an appendix containing key messages regarding food, nutrition and environmental sustainability. These recommendations include advice to: try to eat seasonal produce; reduce food and packaging waste; and avoid overconsuming kilojoules [7]. Several of the Australian Dietary Guidelines form indirect synergies between eating a diet for good health and a sustainable diet to reduce burden on the environment (represented graphically in Figure 1). For example, the overconsumption of kilojoules is associated with overweight and obesity, but is also creating an avoidable environmental burden due to the resources used in the production, storage and preparation of food [7,15,16]. While attempts to create awareness of the impact of dietary choices on the environment exist, the absence of set guidelines relating to sustainable diets in Australia is the probable result of limited evidence in this area of nutrition and no dietary assessment method to accurately measure an individual’s healthy and sustainable dietary behaviours.

**Figure 1 nutrients-07-05226-f001:**
[figure not shown]
Graphic representation of the direct synergies between the 2013 Australian Dietary Guidelines and sustainable dietary behaviours outlined in the Australian Dietary Guidelines [7].

There is no agreed definition for what constitutes a “healthy and sustainable diet”. Separately, healthy diets conform to the Australian Dietary Guidelines [7], while sustainable diets have been defined by the Food and Agriculture Organization of the United Nations as “those diets with low environmental impacts which contribute to food and nutrition security and to healthy life for present and future generations. Sustainable diets are protective and respectful of biodiversity and ecosystems, culturally acceptable, accessible, economically fair and affordable; nutritionally adequate, safe and healthy; while optimizing natural and human resources.” [4]. Several European countries have developed guidelines for a healthy and sustainable diet [17,18] and research examining associations between other dietary recommendations and dietary patterns and their associations with environmental sustainability is becoming available [3,13]. Even with strengthening evidence on the health benefits of diets with lower environmental impact, the revised Australian Dietary Guidelines failed to include specific sustainable eating dietary recommendations [3,19].

There is a plethora of evidence suggesting climate change and poor health are two major public health concerns, both of which would benefit from government policy promoting more sustainable dietary behaviours [2,9,20,21]. However, dietary recommendations and policies cannot be developed without an evidence base. In order to collect evidence on how current dietary patterns adhere to a sustainable diet, surveillance and monitoring of individual dietary behaviours using a comprehensive dietary assessment method is required.

To the authors’ knowledge there is no feasible dietary assessment method to accurately measure an individual’s healthy and sustainable dietary behaviours and the need for such a method has been highlighted in a recent review by Johnston *et al.* [22]. To date methods of dietary assessment have focused mostly on nutrients and food groups and not considered the assessment of sustainable dietary practices, such as reducing food packaging and waste. Brief assessment instruments, commonly used in population surveillance, have been used to reliably estimate the quality of diets in Australia [23]. These methods typically use a short questionnaire or several questions to assess knowledge and specific diet and nutrition behaviours [24,25]. Other frequently used dietary assessment methods, such as written food records, provide more objective data on what individuals are eating and in some cases individuals may be asked to record food waste. However, a limitation of written food records is there is no way to verify the recording and researchers must rely on good literacy levels, the ability of people to accurately estimate portion sizes and remember to write down all meals, snacks and beverages, creating burden on participants. The use of technology in dietary assessment, and more specifically image-based food records, is a new and rapidly emerging area that will reduce the burden for participants through the elimination of detailed writing and portion size estimation. Image-based dietary assessment methods, including the mobile food record (mFR) application, enable people to capture their intake by taking a momentary image and do not allow users to review, edit or alter earlier images [26,27,28,29,30]. This feature may reduce the chances of people reflecting on their prior consumption and consequently underreporting further intake. In addition, before and after eating images taken using the mFR application allow for the assessment of plate waste and packaging use, as well as the estimation of serving and portion sizes. For such reasons the existing mFR application shows great potential as a feasible method for individual and population-wide nutrition monitoring of sustainable dietary behaviours. Food image data previously collected from a population-based sample of adults using the mFR will enable the validation of a *Healthy and Sustainable Diet Index.*

Diet quality indices assist in translating intake data collected using dietary assessment methods to values or scores that are more easily interpretable and allow for consistent comparisons between groups of interest. Such indices are developed to measure dietary patterns, behaviours and adherence to particular eating recommendations in populations [31]. Diet quality indices consider multiple components of a diet and apply weighting factors to each component to calculate a final diet quality score [32]. Developing and validating indices for use in dietary assessment can assist in guiding nutrition interventions, population monitoring, informing policy makers, monitoring the effectiveness of programs and research [33]. Examples of validated diet quality indices include the Healthy Eating Index [33], Mediterranean Diet Score [34], Diet Quality Index [35], Dietary Guideline Index [31], Dietary Quality Score [36], Australian Recommended Food Score [23] and Dietary Approaches to Stop Hypertension (DASH) Diet Score [37].

Traditionally, dietary indices have been developed to monitor specific or general nutrient intake and predict the effect of dietary behaviours on health outcomes. But, there is increasing need to measure impacts of dietary behaviours on external factors due to the potential negative impact on the future of the food supply (e.g., the environment) [22]. A recent review by Johnston and colleagues highlighted the urgent need to develop innovative approaches to measuring and promoting sustainable diets so consumers and policymakers can become aware of the benefits on individual and population health and the environment [22]. In doing so, the authors emphasised the need for culturally acceptable and locally appropriate indices to accurately assess sustainable diets, suggesting the development of such indices would enable the measurement of a suite of indicators relating to the impact of dietary behaviours on health and the food system to inform policy makers [22]. This paper addresses the gap in the literature by proposing a feasible method to assess multiple elements of a healthy and sustainable diet.

This paper describes the protocol and methodology for a proposed novel dietary assessment method to measure indicators of an individual’s healthy and sustainable diet not typically measured in traditional methods. Due to a lack of consensus of what constitutes a healthy and sustainable diet, the five dietary behaviours selected for assessment were chosen based on the evidence documented in the Australian Dietary Guidelines, and Appendix G on Environmental Sustainability [7]. The five characteristics of a healthy and sustainable diet selected relate to nutritional status and/or future food supplies to maintain good health. As the proposed dietary assessment method uses images to assess healthy and sustainable dietary behaviours, the selection has been confined to those that can be objectively assessed from food and beverage images using a mFR. The five indicators to be assessed using the mFR application include the intake of ultra-processed EDNP foods and beverages, individually packaged foods and beverages, fruit and vegetables (including seasonality), dairy, eggs and meat, and plate waste.

Food intake data, collected using the image-based mFR during the Connecting Health and Technology study, will provide evidence to assist the development of this method and a *Healthy and Sustainable Diet Index*, which will provide evidence for policy makers, health professionals, and others interested in promoting environmental sustainability through dietary recommendations (e.g., the agricultural sector). A validated index to accurately assess healthy and sustainable dietary behaviours, and ultimately gather evidence on individual eating behaviours, is timely and urgent. It is yet to be determined but the mFR may have the potential to be a cost effective method to gather valuable data on healthy and sustainable dietary behaviours, an area of nutrition in need of evidence. The dietary assessment method described in this paper when implemented will provide evidence on current adherence to a healthy and sustainable diet, addressing a gap in the literature both in Australia and globally. This protocol paper outlines the methods used to assess healthy and sustainable dietary behaviours using an mFR, providing detail to assist with further advancements in this field of dietary assessment and allowing for future reproducibility. Importantly, the methods proposed in this paper may address the lack of dietary assessment methods to assess sustainable dietary behaviours, as highlighted in the review by Johnston *et al.* [22].

## 2. Experimental Section

### 2.1. Study Participants

The study sample to be used for developing the proposed methods will consist of 247 adults aged from 18 to 30 years, comprising of 162 (66%) women and 85 (34%) men previously recruited for another study, the Connecting Healthy and Technology study, referred to as CHAT [26]. Recruitment involved sending letters of invitation to 15,000 residents from 57 suburbs (using the Socio-Economic Indexes for Areas) in the Perth Metropolitan Area from the Federal Electoral Roll, a compulsory enrolment system for Australians aged over 18 years. Participants were screened either online, using a survey website, or on the telephone to ensure the inclusion criteria were satisfied (aged between 18 and 30 years and owned a mobile phone). For the original study, potential participants were excluded if they were: (a) unable to attend on four occasions to complete the 6-month randomised controlled trial; (b) studied nutrition; (c) took part in extreme forms of exercise; (d) followed a restrictive diet; or (e) pregnant or breastfeeding. The CHAT study was conducted between July 2012 and June 2013.

The Connecting Health and Technology study was registered on the Australian and New Zealand Clinical Trials Registry (ACTRN12612000250831) and approved by the Curtin University Human Resources Ethics Committee (HR181/2011) and the Western Australian Department of Human Research Ethics Committee (#2011/90).

### 2.2. Study Design

During the Connecting Health and Technology study, participants completed four day mFRs using the CHAT application at baseline and at the end of the 6-month randomised controlled trial. During both visits height and weight data were collected. Participants were asked to capture before and after images of all eating occasions using a mobile device (iPod Touch) provided by the research team. On the initial visit participants were taught how to use the specifically designed dietary assessment method, the CHAT application, uploaded onto the iPod Touch (iOS6). Participants were asked to place a small fiducial marker in the bottom left hand corner of every image to assist in portion size and colour estimation [38]. Details of the mFR CHAT application have been previously described by Kerr *et al.* [39].

Participants were asked to take images over four consecutive days, from Wednesday to Saturday. On completion of the food record, participant’s clarified the contents of images with an Accredited Practising Dietitian, and verified plate waste or if the leftover food or beverage was consumed at a later stage. Each image obtained during the CHAT study contains metadata on the time, date and location it was taken, allowing for the assessment of whether fresh produce were in season at time of consumption. The food images collected during the CHAT study will be used to validate and test the *Healthy and Sustainable Diet Index*.

For the development of the proposed methodology, participants completed an mFR at baseline (*n =* 247) and repeated this six months later (*n =* 220). A secondary analysis by the Accredited Practising Dietitian who was involved in the original analysis of all food images collected during the CHAT study will take place. A purpose built Microsoft Access database will be developed to assess the contents of images, and the review of each image pair (including a before and after eating image). A minimum of one image pair per day will be required to be considered a valid day. Five indicators of a healthy and sustainable diet will be assessed using the images captured using the mFR. An objective of this study is to determine whether the five selected dietary behaviours can be assessed from image-based food records without interaction with participants. This is therefore a “proof of concept” approach to developing the Index before replication in possible future interventions. A flowchart outlining the design of the proposed study can be seen in Figure 2.

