Using the protocol outlined in this paper, the intake of fruit and vegetables will be analysed from each eating image pair and classified according to the Australian Dietary Guidelines serve sizes (1 serve of vegetables = 75 grams, ½ cup cooked vegetables or 1 cup of salad vegetables, and 1 serve of fruit = 150 grams, 1 medium piece or 2 small pieces of fruit). A Microsoft Access database tool will be created to record the estimated serve size and type of fruit and vegetable consumed separately. This feature will allow for further assessment of the environmental impact of different varieties. As the time and date stamp is available from images collected with the mFR, the date fruits and vegetables were consumed can be recorded and merged within the database containing information on when each fruit and vegetable is in season. For example, in Western Australia bananas are in season in summer and autumn, meaning if someone consumed a banana between 1st December and the 30th May then the banana will be recorded as “eaten in season”. For this study, seasonal fruits and vegetables will be classified according to the Western Australia (WA) Seasonal Fruit and Vegetable Calendar [63].

Dietary assessment of seasonal and local fruit and vegetable intake poses significant challenges including: the additional burden of recording “place of origin” at time of purchase; prepared food not carrying this information (e.g., buying a salad at a café): and the sale of fruits and vegetables all year around, regardless of seasonality. A limitation of assessing the intake of seasonal fruit and vegetable intake is that there is no way of determining the origin of fresh produce, for example a banana from Queensland could be eaten in Western Australia, 4341 kilometres away by road (the main transportation method used). However, consuming seasonally available produce, regardless of origin, is likely to reflect an aspect of a healthy and sustainable diet. There is currently limited data on the intake of seasonal fruits and vegetables by adults in Australia. As less than 7% of Australians consume the recommended daily serves of vegetables and less than half consume the recommended two serves of fruit [64], increasing intake alone, regardless of seasonality, would result in health benefits.

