An example of fruit to be consumed can be seen in the mFR image (as it appears using the web application hosted on a secure server) in Figure 5. Using this example containing the date of the image, one serve of fruit (e.g., one medium banana) would be entered in the database and because this eating occasion took place in September in Western Australia, this piece of fruit would be considered eaten “out of season”.

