Each component incorporated into the *Healthy and Sustainable Diet Index*, will be given a weighting used to calculate a final score measuring adherence to a healthy and sustainable diet. For example, typically indices have a maximum score of 100, with a higher score indicating greater adherence to the preferred dietary pattern [23]. Individual components will be given a weighting to reflect consistency with the recommended dietary and sustainable eating outcomes, for example, fruit and vegetable intake may be given a higher weighting as it contributes to both healthy and sustainable eating.

The theoretically driven *Healthy and Sustainable Diet Index* will be internally validated for reliability, content validity and construct validity using 4-days image-based food records collected during a 6-month randomised controlled trial. The baseline data collected during the CHAT study (*n =* 247) will be randomised into thirds using age- and sex-stratified random sample techniques. Two-thirds of the sample will be randomly selected as the derivation cohort and the image-based mFRs of those selected will be used to develop the *Healthy and Sustainable Diet Index* using regression techniques. The remaining one-third of the sample will be used as the validation cohort for the *Healthy and Sustainable Diet Index*. This Index will also be used in the assessment of food images from the 6-month follow up (*n =* 220), and the results compared with baseline.

To assess content validity, components of the *Healthy and Sustainable Diet*
*Index* will be assessed against the Australian Dietary Guidelines [7]. Construct validity will quantitatively assess how well the Index measures conformance to a healthy and sustainable diet.

To determine a total score using the *Healthy and Sustainable Diet Index*, density scores for each component will be calculated. Internal consistency, one form of reliability, will be assessed using Cronbach’s coefficient α. This test has previously been used in the evaluation of the Healthy Eating Index [70] to examine the degree of association between components, to determine if a diet only has one dimension. The relationship between the components of the *Healthy and Sustainable Diet Index* will be assessed using Pearson correlations coefficient. Principle component analysis will be used to assess if there are independent components of the Index. This will measure if there are any significant independent predictors of an overall score.

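### The named coder has prior involvement in CHAT and the worked example shows the image date, so coder expectation or drift could bias the secondary baseline versus 6-month comparison of the Index

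*Protocol article*

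**What the plan says.** **Who codes.** Section 2.2 of the protocol article plans "A secondary analysis by the Accredited Practising Dietitian who was involved in the original analysis of all food images collected during the CHAT study". No second coder is mentioned. The same section says that, during the trial, participants "clarified the contents of images with an Accredited Practising Dietitian, and verified plate waste"; it does not say whether this was the same dietitian.

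**What the coder can see.** Section 2.2 also states: "Each image obtained during the CHAT study contains metadata on the time, date and location it was taken". Section 2.3.3 (Fruit and Vegetables) presents an image as displayed in the web application and codes it from its date: "Using this example containing the date of the image, one serve of fruit (e.g., one medium banana) would be entered in the database". The fruit is then classed as out of season because the month was September. Earlier in 2.3.3, season is obtained by linkage: "the date fruits and vegetables were consumed can be recorded and merged within the database" that holds the seasonal calendar. The coding database is still to be built (section 2.2), and its screen is not described.

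**What the coding feeds.** Section 2.5 derives and validates the Index on baseline data only, split two-thirds to one-third of n = 247. It then adds: "This Index will also be used in the assessment of food images from the 6-month follow up" (n = 220), with results compared with baseline. The only reliability statistic named there is Cronbach's alpha across Index components.

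**The concern.** The quantities coded are estimates: serves, approximate weights or volumes, and the percentage of food left on the plate. Estimates of this kind can move with the coder's standard, which may drift over a long coding task, and with what the coder expects to see at a given visit. A systematic shift between the two sets of records adds directly to the mean change in the Index. It does not shrink as the sample grows.

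At stake is the interpretation of the 6-month comparison. If the visit can be told from the screen, or if the two visits are coded in separate blocks, a difference between them could be dietary change, a change in coding, or both. Cronbach's alpha does not help here: it describes how the components hang together within a score, not whether the same image would be coded the same way on another occasion.

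**Working it through.** The plan gives no figure for coder error or agreement, so there is nothing to reproduce. The check has two parts.

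**1. Does a visible date reveal the visit?**

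- Inputs: CHAT was conducted between July 2012 and June 2013 (section 2.1); records were taken at baseline and 6 months later (section 2.2).
- Assumption: the stated window covers all baseline and all follow-up records.
- Earliest possible follow-up: July 2012 + 6 months = January 2013.
- Latest possible baseline: June 2013 − 6 months = December 2012.
- Result: baseline records fall in about July to December 2012 and follow-up records in about January to June 2013. The two ranges do not overlap, so the date identifies the visit apart from a few records near the turn of the year if the interval was not exactly six months. The September image in 2.3.3, if it comes from CHAT, could only be a baseline record.
- If the window does not cover all records, some overlap is possible and the date is a less complete guide.

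**2. What size of coder shift would matter?**

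This is a detection threshold, not an estimate of bias.

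- Input from section 2.5: n = 220 at follow-up, that is 220/247 = 89.1% of baseline. All 220 are taken to have a usable baseline record.
- Assumptions: a 100-point Index (section 2.5 mentions this only as typical of indices) and a within-person SD of change of 10 to 20 points (not in the article).
- SE of mean change = SD/√n, with √220 = 14.83.
- SD 10: 10/14.83 = 0.67; 1.96 × SE = 1.32 points.
- SD 20: 20/14.83 = 1.35; 1.96 × SE = 2.64 points.

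With no true change in diet, a constant coder shift equal to 1.96 × SE would centre the test statistic on the two-sided 5% critical value, so it would give a nominally significant result about half the time. A larger shift would do so more often. Nothing in the article says whether a shift of this size is likely.

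**The case against.** The strongest reply is that this rests largely on silence. The article does not say that coding is unmasked, in what order records are coded, or what the Access screen will show. It is a condensed account, and a fuller protocol may deal with these operational details. The image in 2.3.3 illustrates seasonality in the web application; it does not specify the coding screen. Linkage of date to season is already foreseen. The affected comparison is secondary in a proof-of-concept project, and no test of change is stated.

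Much of this stands, and it limits the point. What remains is that the one workflow the article does illustrate has the date on view and used in coding, that the named coder was involved before, and that a comparison between visits is planned.

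A reader might also infer more than the text allows:

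- *That coding is unmasked to trial arm.* The listed metadata are time, date and location; nothing is said about the coder's knowledge of allocation, and no comparison by arm is planned.
- *That bias enters the comparison.* It could. Drift becomes confounded with visit if the visits are coded in separate blocks, and the order is not given.
- *That one person makes every judgement on every image.* In the sentence naming the dietitian, the reference to all food images may belong to the earlier analysis or to the new one, and other coders are not excluded.
- *That the validation of the Index is compromised.* The derivation and validation cohorts are both drawn from baseline, so a shift between visits does not touch them.

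**Conclusion.** The concern holds in a limited form. A coder with prior involvement, working from images displayed with their dates, could tell the visit for nearly all records, and coder expectation or drift could then bias the secondary baseline versus 6-month comparison of the Index. This rests on two assumptions: that the July 2012 to June 2013 window covers all records, and that the coder's view resembles the web application example.

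The size of any bias is unknown. The range of 1.32 to 2.64 points says only how large a shift would have to be to reach 1.96 standard errors under an assumed scale and SD. The point does not extend to the baseline derivation and validation split or to any arm comparison. It is worth acting on because the coding database has yet to be built and the safeguard costs little.

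**What to change.** Add to section 2.2:

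- Whole 4-day records from baseline and 6 months will be coded in one randomly mixed sequence, each under a random record code. The days of a record stay together, so that leftovers eaten later can still be followed.
- Date and visit will be hidden from the coder where the software allows.
- Season will be assigned by the database from the time stamp after coding is complete, which 2.3.3 already permits, since dates can be "merged within the database containing information on when each fruit and vegetable is in season". The worked example in 2.3.3 should be reworded to match.

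The mixed order is the more important part: it removes drift as an explanation for change even if the date cannot be hidden. Hiding the date and visit reduces the scope for expectation.

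The cost is slight: set-up of a random work list and possibly an adjustment to the image display, with no extra staff or data. The dietitian may still recognise some records, so masking will not be complete.
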